### Data analysis

The primary program evaluation question is whether the depression treatment program results in improved HIV and mental health outcomes for patients with HIV and depression relative to the standard of care prior to program implementation. The main analysis will follow an “intent-to-treat” approach, classifying patients according to screening vs. treatment phase (unexposed vs. exposed to the program) without regard to actual treatment received. In our main analysis, we will define our primary outcome, retention in HIV care with viral suppression 6 months after starting ART, as never being more than 30 days late to any scheduled return visit in the first 6 months on ART and having a viral load < 1000 copies/mL at 6 months; patients not retained or not suppressed will be coded as a failure. (Table 2**)** This composite outcome was chosen as the primary outcome because it is the definition of ART clinical success in the Malawian ART treatment system; those not retained and those retained but not suppressed are both clinical failures. This main analysis will estimate the probability of retention and viral suppression 6 months after starting ART using a generalized linear model with binomial error distribution, adjusting for calendar time and potential confounders that are imbalanced between arms at baseline, potentially including age, sex, clinic, PHQ-9 score, and presence of suicidal ideation. We will model these associations using separate generalized linear models among two samples: (a) those with mild, moderate, or severe depression (PHQ-9 ≥ 5) and (b) those with moderate to severe depression (PHQ-9 ≥ 10).

**Table 2 Tab2:** Outcome Variables

	Definition	Type
Primary Outcome		
Retention with Viral Suppression	both attending all ART appointments “on time” through 6 months and having a viral load < 1000 copies/mL at 6 months	Binary
Secondary Outcomes		
Viral Suppression	viral load < 1000 copies/mL at 6 months	Binary
Retention	attending all ART appointments “on time” through 6 months	Binary
	number of ART appointments attended through 6 months	Count
Consistent ART supply	Never going more then 5 days without ART, as calculated from pills dispensed and time between attended appointments	Binary
Depression Remission	PHQ-9 Score < 5 at 6 months	Binary

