### Timeline

The screening phase began at Clinic A in April 2017 and Clinic B in May 2017. The treatment phase was integrated into Clinic A after 7 months, in November 2017, and into Clinic B after 11 months, in April 2018. Identification of new patients concluded at both clinics in November 2018. Follow-up data abstraction is expected to continue through June 2019.

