## Discussion

This novel pilot program is Malawi’s first depression treatment program for people living with HIV and one of the few in the sub-Saharan Africa region to use a task-shifting model to provide both problem-solving therapy and antidepressant depression treatment [34–38]. This study will be the first to evaluate the impact of such a program on both mental health and HIV outcomes and to investigate the potential benefits of this task-shifting depression care model. Findings from this study will directly inform the Malawi Ministry of Health’s ongoing national strategic plans on mental health.

The study design draws both from implementation science and epidemiologic methods, with the ultimate goal of generating evidence-based practices, interventions and policies that can readily (and rapidly) be adopted and integrated into routine care in public sector settings [59–61]. We have conscientiously designed the evaluation to yield high quality, real-world findings on integrating depression management into HIV care that are readily applicable to the implementation of integrated mental health services in non-specialist settings.

The program itself focuses on provider training to manage antidepressants and provide evidence-based counselling, and thus cannot be randomized at the individual level. Since patients do not see the same provider from one appointment to the next, in this context the intervention could not be randomized at the provider level either. A cluster-randomized trial was also beyond the resources available for this project. Given these constraints, a multiple baselines design provides stronger causal inference than would be available with a simple pre-post design. Multiple baseline designs have been advocated as one of the designs providing the strongest causal inference apart from the randomized trial [62].

We anticipate that the study will generate evidence on the effect of depression management on HIV outcomes and the feasibility of integrating depression management into existing HIV care clinics. The results of the study will inform practice and policy decisions on integration of depression management in HIV care clinics in Malawi and similar low-income country settings, allowing design of a scale up strategy.

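### Clinic is fixed by the staggered design, yet the primary model includes it, like every covariate except calendar time, only if it looks imbalanced at baseline

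*Protocol article*

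**What the plan says.** The main analysis in the Data analysis section compares phases, "classifying patients according to screening vs. treatment phase (unexposed vs. exposed to the program) without regard to actual treatment received". It estimates the probability of retention with viral suppression "using a generalized linear model with binomial error distribution". Calendar time is an unconditional adjustment. Beyond it, the model takes in "potential confounders that are imbalanced between arms at baseline, potentially including age, sex, clinic, PHQ-9 score, and presence of suicidal ideation". The section gives no criterion for imbalance and does not make clinic a fixed term.

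The rule is applied twice: "We will model these associations using separate generalized linear models among two samples", namely PHQ-9 ≥5 (n=502) and PHQ-9 ≥10 (n=131).

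The Timeline section gives the stagger: "The screening phase began at Clinic A in April 2017 and Clinic B in May 2017", and "The treatment phase was integrated into Clinic A after 7 months, in November 2017, and into Clinic B after 11 months, in April 2018". Accrual ended at both clinics in November 2018. The Discussion rests the causal argument on this layout, saying that "a multiple baselines design provides stronger causal inference than would be available with a simple pre-post design".

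**The concern.** Phase was not randomised, so the adjustment set carries the causal claim. The advantage of a multiple-baseline design over a simple pre-post comparison is that each clinic serves as its own baseline while the other clinic shows what time alone does. That contrast needs a clinic term. The article treats clinic as a possible chance imbalance, although the crossover schedule itself ties clinic to phase.

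Adjusting for calendar time makes the clinic term more important. Once time is in the model, the phase effect is learned largely from the months in which the two clinics were in different phases. In those months, phase and clinic are the same variable.

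The other covariates raise a lesser issue. Confounding needs both imbalance and prognostic strength, and the rule looks only at imbalance. Baseline PHQ-9, which defines both analysis populations, could be left out because it happened to look balanced.

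**Working it through.** **Benchmark: the plan's own figure.** Population and sample size states 80% power for 60% vs 72% at n=502. Assume a two-sided 5% test and equal groups of 251 (neither is stated). The pooled proportion is 0.66. The null SE is √(2×0.66×0.34/251) = 0.0423 and the alternative SE is √((0.60×0.40+0.72×0.28)/251) = 0.0419. Then z = (0.12 − 1.96×0.0423)/0.0419 ≈ 0.885, and power is 81.2%. For n=131 and 60% vs 82%, the same method gives 79.9%. Both figures reproduce, so 12 points and 22 points are fair yardsticks for bias.

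**Layout from the Timeline dates** (November 2018 counted as a full month)

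| | Screening months | Treatment months |
|---|---|---|
| Clinic A | 7 | 13 |
| Clinic B | 11 | 8 |
| Total | 18 | 21 |

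With equal monthly accrual (assumption), Clinic A's share is 7/18 = 39% in screening and 13/21 = 62% in treatment, a gap of 23 points. With Clinic A's share of accrual varied from 30% to 70%, and November 2018 counted or not, the gap is 19 to 24 points, a standardised difference of 0.43 to 0.50.

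**Share of a clinic difference absorbed if clinic is omitted.** On the risk-difference scale this is the coefficient of phase when clinic is regressed on phase and the time terms in the model, with cells weighted by accrual.
- Linear calendar time: 0.64 to 0.79 (0.76 for equal accrual in the layout above).
- Month effects: 1.00 exactly. Phase varies within a month only from November 2017 to March 2018, when Clinic A was in the treatment phase and Clinic B was not. Within those months phase equals clinic.

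Bias is this share times the clinic difference in outcome, which the documents do not give:

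| Assumed clinic difference | Linear time | Month effects |
|---|---|---|
| 0 points | 0 | 0 |
| 5 points | 3.2 to 4.0 | 5 |
| 10 points | 6.4 to 7.9 | 10 |
| 15 points | 9.6 to 11.8 | 15 |

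**Would the rule admit clinic?** This depends on a criterion that is not stated.
- Assumed p<0.05 test, n=502: clinic is flagged more than 99% of the time.
- Same test, n=131, equal accrual (60.5 vs 70.5 patients): null SE 0.0876, alternative SE 0.0853, z = (0.230 − 1.96×0.0876)/0.0853 ≈ 0.68, so clinic is flagged 75% of the time. Over the range of layouts this is 67 to 80%, so clinic is omitted in about 20 to 33% of cases.
- Assumed standardised difference above 0.1, n=131: the SE is about √(1/60.5+1/70.5) = 0.175. Then (0.47 − 0.10)/0.175 ≈ 2.1, so clinic is flagged about 98% of the time.

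**Other covariates.** Take a true imbalance of 0.15 SD and 232 vs 270 patients, so SE = √(1/232+1/270) = 0.0895. A 5% test flags it 39% of the time at n=502 and 14% at n=131. A 0.1 threshold flags it about 71% of the time at n=502. Under the 5% test, bias remains only when the covariate is not flagged. The expected unadjusted imbalance is then 0.15×[Φ(0.28) − Φ(−3.64)] − 0.0895×[φ(0.28) − φ(3.64)] ≈ 0.058 SD. With assumed outcome slopes of 5 to 15 points per SD, the average residual bias is 0.3 to 0.9 points, small against 12.

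**Precision cost of a fixed clinic term.** The variance inflation of the phase effect, 1/(1−R²) for phase on the other terms, is 2.8 to 3.0 with linear time alone and 3.5 to 3.7 with clinic added. For equal accrual, 3.60/2.87 = 1.25 in variance, so the standard error is √1.25 = 1.12 times as large.

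**The case against.** The strongest reply is that the stated rule would catch clinic because the schedule makes it imbalanced. For the primary population this largely stands: at n=502 any ordinary criterion would admit it. A reader might infer that the primary estimate will be computed without clinic; the documents do not support that. The remaining risk is mainly in the PHQ-9 ≥10 model, which the article calls the secondary population of interest, and there it depends on the unstated criterion.

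A second reply is that the imbalance criterion and the final covariate list belong in an analysis plan, which is not shown. That is fair for the threshold. But conditional entry is a rule the article states, and it applies that rule to a design factor.

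Three further inferences go too far.
- Multiplying the 23-point gap in clinic share by a 10-point clinic difference gives only 2.3 points of bias. That describes a model without calendar time, which is not the model planned.
- One might expect intervals after such selection to be too narrow. Selection here is on the relation of covariate to phase, not on the outcome. Simulations with 232 vs 270 patients, one covariate, no calendar time and no programme effect gave rejection rates of 4.8 to 5.5% with selection and 4.5 to 5.8% with adjustment always made.
- Different covariate sets in the two samples are not an error in themselves. The article plans separate models and promises no formal comparison between them.

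**Conclusion.** The point holds as a flaw in the stated rule. Clinic is part of the design, and with calendar time always in the model the phase contrast depends on it, so its inclusion should not be left to an imbalance check.

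If clinic were omitted, 64 to 79% (linear time) or 100% (month effects) of any clinic difference in outcome would pass into the programme effect. That is about 6 to 10 points for a 10-point difference. These figures assume constant accrual, a Clinic A accrual share of 30 to 70%, and a clinic difference that the documents do not give.

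The expected effect on the n=502 result is small because clinic would almost surely enter. At n=131, omission is a 20 to 33% risk under an assumed 5% test and about 2% under an assumed 0.1 standardised-difference threshold. For age, sex, PHQ-9 score and suicidal ideation, the expected cost is small residual bias, some lost precision and an adjustment set that depends on the data.

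**What to change.** Reword the covariate sentence in Data analysis so that both models always include clinic and calendar time, together with age, sex, baseline PHQ-9 score (continuous) and suicidal ideation, regardless of observed balance. Delete the condition that confounders be imbalanced between arms at baseline, and the word potentially before the list.

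This is one sentence, and it uses only variables the article already names. The cost is precision: with linear time, the clinic term raises the variance inflation of the phase effect from about 2.8–3.0 to about 3.5–3.7. The added terms weigh more at n=131 than at n=502. That loss is the price of estimating the multiple-baseline contrast on which the Discussion relies.

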#### Secondary

**H2** Compared to the period prior to the depression treatment program, adults with HIV and depression during the implementation of the treatment program will be more likely to be virally suppressed 6 months after ART initiation.

**H3** Compared to the period prior to the depression treatment program, adults with HIV and depression during the implementation of the treatment program will be more likely to be retained in HIV care 6 months after ART initiation.

**H4** Compared to the period prior to the depression treatment program, adults with HIV and depression during the implementation of the treatment program will have higher HIV care appointment adherence (proportion of scheduled visits that were attended) over the first 6 months on ART.

**H5** Compared to the period prior to the depression treatment program, adults with HIV and depression during the implementation of the treatment program will be more likely to have achieved depression remission 6 months after ART initiation.

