### Measures

We are abstracting data on HIV and mental health outcomes for patients newly initiating ART who screen positive for depression (Table 1).

**Table 1 Tab1:** Measures

	Measure	Source	Time Point
Viral Load	viral load copies/mL	Mastercard or EMR	6 month
Appointment Attendance	Appointment Dates	Mastercard or EMR	Monthly
Depressive severity	PHQ-9 Scores	Mastercard	Monthly

*EMR* Electronic Medical Record

Depressive severity is being measured using the Chichewa version (vernacular language for Malawi) of the Patient Health Questionnaire (PHQ)-9. The score of 5–9 on the PHQ-9 is considered mild depression while that of 10 and above is moderate to severe depression [40]. Providers screen all patients for depression at the time of ART initiation by administering the PHQ-9 rather than self administration because of the low literacy levels among the patients. Patients who score ≥ 5 at ART initiation are re-assessed with the PHQ-9 by the HIV provider at each subsequent ART visit. This information is captured on a form called the Mental Health Mastercard that is kept with the patient’s HIV file.

Depression Remission will be defined as a PHQ-9 score < 5 at 6 months.

Retention in HIV care will be defined as being “on time” to all scheduled ART return visits in the first 6 months on treatment. “On time” will be defined as no more than 30 days late; a secondary, tighter definition will define “on time” as no more than 14 days late At ART initiation and each subsequent ART appointment, providers give patients a follow-up appointment date and a sufficient supply of ART. This information is recorded in the patient’s chart, called an HIV Mastercard, and in the Electronic Medical Record (EMR). However, generally for the first 6 months of care, new ART patients receive a 30-day supply of ART and a return appointment date in 30 days. Most often, patients need to attend monthly ART refill appointments for their first 6 months of care in order to maintain ART supply through 6 months.

Consistent ART supply will be defined as never going more than 5 days without ART in the first 6 months, calculated from the days’ supply of ART dispensed at each appointment in the first 6 months and the time between appointments.

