### Population and sample size

We are abstracting screening data for all consenting adult (≥18 years old) patients newly initiating ART and screened for depression at the time of ART initiation at the study sites during the study period. Additional depression treatment and outcome data are being abstracted for all patients who screen positive for mild, moderate, or severe depressive symptoms (PHQ-9 total score ≥ 5) [56, 57].

We focused on two populations of interest. For the primary population of interest, all patients with depressive symptoms (PHQ-9 score ≥ 5), the original sample size was determined to provide 80% power to detect an 11 percentage point pre-post difference in the primary outcome. For the secondary (smaller) population of interest, all patients with moderate to severe depression (PHQ-9 score ≥ 10), the original sample size would provide the same power to detect an 18 percentage point pre-post difference. To achieve this power, we would require 645 patients with any depressive symptoms and 225 patients with moderate to severe depressive symptoms.

Based upon the historical rate of new ART patients (122 per month between the two clinics) and the expected prevalence of any depressive symptoms (35%) and moderate to severe depressive symptoms (12%) based on prior literature [58] [7], we originally planned for a 15-month data collection period to accrue the targeted sample. During the course of data collection, the rate of new ART patients was higher than expected but the prevalence of depressive symptoms was lower than expected. After extending the recruitment period for an additional 5 months, the accrual of new ART patients concluded with a final sample of 2084 individuals. The prevalence of mild to severe depression was 24.1% (*n* = 502) and the prevalence of moderate to severe depression was 6.3% (*n* = 131). This sample has 80% power to detect a slightly larger difference in the primary outcome of 12 percentage points (e.g. 60% vs. 72%) or a risk ratio of 1.2 for those with mild to severe depression. For those with moderate to severe depression, the sample has 80% power to detect an improvement in the primary outcome of 22 percentage points (e.g. 60% vs. 82%) or a risk ratio of 1.4.

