### Data abstraction and management

Data on viral loads, HIV appointment attendance, and depressive symptoms is abstracted from electronic and paper medical records and the depression treatment registry at the sites. ART appointment data including the date of the appointment, the expected return date, and medication prescribed is recorded in the EMR, on a paper patient file (called an HIV Mastercard), or both. The results of the viral load tests are recorded in the EMR. Data on patients’ depressive symptoms and depression treatment are only recorded on paper in an additional patient filed attached to the ART mastercard (called a mental health mastercard). The community health workers responsible for administering the Friendship Bench problem-solving therapy also maintain paper records (called a Counselling Mastercard) that capture engagement with the PST sessions. Cost information was collected using a time-audit approach to estimate costs of delivering the program, including the opportunity cost of training participation and the time providers and supervisors spend to deliver and supervise the program. Time-audit data was captured through a combination of direct observation of medical provider and counsellor encounters supplemented with self-reporting by counsellors.

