In secondary analyses, we will consider ART care retention through 6 months (binary), number of ART appointments attended in the first 6 months (count), maintaining consistent ART supply through 6 months (binary), and viral suppression at 6 months among those retained (binary). Further, secondary analyses will take an “as treated” approach, comparing patients who receive treatment in the treatment phase to all patients during the screening phase; and an “as adequately treated” approach, comparing patients who receive adequate treatment (≥3 consecutive months of protocol-concordant antidepressant prescriptions or ≥ 4 counseling sessions) during the treatment phase to all patients during the screening phase. Data are not available on antidepressant adherence. (Table 3).

**Table 3 Tab3:** Analyses

Analysis	Definition
Primary: “intent-to-treat”	Initiated after program launch
“as treated”	Received depression treatment
“as adequately treated”	≥3 consecutive months of protocol-concordant antidepressant prescriptions or ≥ 4 counselling sessions

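### H4 is defined as the proportion of scheduled visits attended, but the only matching outcome listed is a raw count of visits with no denominator

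*Protocol article*

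**What the plan says.** The secondary hypotheses in the Protocol article state that patients in the programme period will have "higher HIV care appointment adherence (proportion of scheduled visits that were attended) over the first 6 months on ART". That is a ratio with a patient-level denominator.

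Table 2 (Data analysis) lists the outcomes. H1, H2, H3 and H5 each have a matching row: retention with suppression, suppression, retention and remission. For H4 the only candidate is a second line under Retention, "number of ART appointments attended through 6 months", of type Count. The secondary-analysis text that follows names "number of ART appointments attended in the first 6 months (count") and mentions no proportion, rate or offset.

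Three other statements bear on whether the difference matters:

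- Measures says that, generally, "new ART patients receive a 30-day supply of ART and a return appointment date in 30 days", and adds: "Most often, patients need to attend monthly ART refill appointments for their first 6 months of care". Both statements are qualified, so the schedule is usual rather than fixed.
- Measures also says how dates arise: "At ART initiation and each subsequent ART appointment, providers give patients a follow-up appointment date and a sufficient supply of ART".
- Data abstraction and management says: "ART appointment data including the date of the appointment, the expected return date, and medication prescribed is recorded". The raw material for a denominator therefore exists.

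**The concern.** The article is not silent on H4. It gives two different variables for it, one in the hypothesis and another in the outcome table and analysis text. A reader cannot tell which one decides H4, and the choice could be made after the results are seen.

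The two variables answer different questions. The proportion asks how reliably patients kept the visits they were given. The count also depends on how many visits they were given. The comparison is between patients who started ART before and after programme launch, without randomisation, so nothing in the design makes visit spacing equal in the two phases. If spacing differed, the count would differ even with identical adherence.

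**Working it through.** The article states no sample size, power or effect size for H4, so there is no figure to reproduce. Its power statement concerns a different endpoint: "This sample has 80% power to detect a slightly larger difference in the primary outcome of 12 percentage points".

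**Step 1. When the two measures agree.** Write S for the number of visits scheduled in 6 months and p for the proportion attended. Then count = S × p. With 30-day intervals over 180 days, S = 180/30 = 6. If S = 6 for everyone, count = 6p and the two measures carry the same information. The 30-day interval is the article's usual schedule; 180 days is used here for 6 months.

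**Step 2. When S varies.** The article names no interval other than 30 days, so the longer ones here are assumptions. At full adherence (p = 1):

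| Interval | S | Count | Proportion |
|---|---|---|---|
| 30 days | 6 | 6 | 100% |
| 60 days (assumed) | 3 | 3 | 100% |
| 90 days (assumed) | 2 | 2 | 100% |

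**Step 3. Effect on a phase comparison.** Assume 85% attendance in both phases and no 60-day intervals in one phase. Let a share s of patients have 60-day intervals in the other phase. Mean count = 0.85 × [6(1 − s) + 3s].

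| s | Mean count | Ratio to s = 0 | H4 proportion |
|---|---|---|---|
| 0% | 0.85 × 6.0 = 5.10 | 1.00 | 85% |
| 10% | 0.85 × 5.7 = 4.85 | 0.95 | 85% |
| 20% | 0.85 × 5.4 = 4.59 | 0.90 | 85% |

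The shift could run in either direction between phases. Nothing in the article says that s differs from zero.

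**Step 4. Lateness.** Because each next date is set at the visit attended, a patient who comes 14 days late to every 30-day visit completes 180/(30 + 14) = 4.09, that is 4 visits. The count is 4 rather than 6, although every visit scheduled was eventually attended.

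**Step 5. What a naive denominator would do.** The same scheduling rule means that a patient lost to care stops generating return dates. Take 30-day intervals and a patient who attends one return visit and then disappears. Recorded dates give 2 scheduled and 1 attended, so 1/2 = 50%. Continuing the schedule to 6 months gives 1/6 = 17%. A patient lost after five return visits scores 5/6 = 83% either way. The distortion therefore falls on early loss, and Background says that most loss occurs after the first visit or within the first few months. A count model with an offset built only from recorded return dates has the same weakness.

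**The case against.** The strongest reply is that the count is good enough. Under the usual monthly schedule it is close to six times the proportion, and a count over a fixed 6-month window shows early loss plainly, which a carelessly built proportion would hide. The model form for a secondary outcome is also commonly left to an analysis plan that is not shown. Retention is covered in addition by the binary on-time definitions (30 and 14 days) and by consistent ART supply. Much of this stands. The count is probably a close proxy, and the point about early loss changes what a sound repair looks like. It does not remove the mismatch, because the article itself fixes one variable in H4 and another in Table 2.

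A reader might infer more: that the programme adds visits, since patients on antidepressants are reviewed every four weeks, and so inflates the count. The documents do not support this. The section on algorithm-based care places that review at the monthly ART appointment. Intervention program describes symptom monitoring in the screening phase as well. Counselling sessions are recorded on a separate form, while Table 2 counts ART appointments only. Nothing says that the programme changes how ART visits are scheduled.

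A reader might also take the 5% or 10% in the illustration as an estimate of bias. It is not one. The article gives no information on intervals longer than 30 days or on any difference between phases, and only a difference between phases would bias the comparison.

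Rewording H4 to the count would also end the contradiction, but the study would then no longer assess adherence as H4 now defines it.

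**Conclusion.** The point holds as a mismatch of definition: as written, the plan does not estimate the quantity H4 names. That conclusion needs no assumption. The practical consequence is uncertain and may be negligible. It is zero if visit spacing is the same in both phases. Under the assumed shifts of 10 and 20 percentage points to 60-day intervals it would be about 5% and 10% of the mean count. Only H4, a secondary hypothesis, is affected. H1, its composite outcome and the sample size are untouched. The correction should be made because it is cheap, the dates are already recorded, and it settles which variable decides H4 before results are seen.

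**What to change.** In Table 2 and in the secondary-analysis paragraph, define the H4 outcome as visits attended divided by visits scheduled in the first 6 months. Analyse it as grouped binomial with robust standard errors. Keep the number of visits attended as a supporting description, and report beside it the mean number scheduled by phase, so that readers can see whether spacing differed.

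State the denominator rule: after a missed visit or loss to care, scheduled visits continue to accrue to 6 months at the patient's last assigned interval, usually 30 days. This stops early dropouts from receiving a small denominator. Do not use a denominator or offset built only from recorded return dates. The rule should also say when a late return counts as missed; the 30-day lateness limit already in Measures could serve.

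The cost is one table row, one analysis sentence and one derivation rule. No new data are needed, because appointment dates and expected return dates are already recorded.

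### H2 concerns viral suppression in all patients with depression, but the planned analysis keeps only those retained, a group the programme is expected to change

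*Protocol article*

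**What the plan says.** H2, among the secondary hypotheses, is about adults with HIV and depression and predicts that those in the programme period "will be more likely to be virally suppressed 6 months after ART initiation". It sets no condition on retention. Table 2 defines the outcome in the same unrestricted way, as "viral load < 1000 copies/mL at 6 months".

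The secondary-analysis paragraph of the Data analysis section is the only text that says how this outcome will be analysed, and there it becomes "viral suppression at 6 months among those retained (binary").

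Retention has a strict definition in Measures: "Retention in HIV care will be defined as being “on time” to all scheduled ART return visits in the first 6 months on treatment", where on time means no more than 30 days late. H3 then predicts that patients in the programme period "will be more likely to be retained in HIV care 6 months after ART initiation".

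For the primary composite, the Data analysis section protects against selection with an explicit rule: "patients not retained or not suppressed will be coded as a failure". No such rule is stated for viral suppression as a separate outcome.

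**The concern.** The article gives two populations for one secondary outcome. This is a conflict on the page, not a detail left to an analysis plan.

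The population in the Data analysis section is also the weaker choice. It is defined by something that happens after ART starts and that the programme is meant to alter. If the programme keeps in care some patients who would otherwise have dropped out, the retained patients of the treatment phase are a different mix from those of the screening phase. Comparing suppression between the two then combines any real effect with a change in who is counted. The intent-to-treat classification by phase does not prevent this, because the selection happens within each phase.

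The strict definition adds a second problem. A patient 35 days late to one visit, still in care and with a suppressed 6-month viral load, has the outcome measured but is left out. That patient fails H1 and would succeed on H2, so H2 in all patients is not a repeat of the primary outcome.

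At stake is the reading of a secondary result in a study meant to inform national mental health planning.

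**Working it through.** The plan gives no figure for suppression among the retained, so there is none to reproduce. The check illustrates direction and size.

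**Inputs**
- Background: 76% retained at 12 months; 65% both retained and suppressed. These are 12-month figures for all adults starting ART, used as stand-ins for 6-month figures in patients with depression.
- Screening-phase retention R0 = 0.76. Suppression among the retained v = 0.65/0.76 = 85.5%.
- Assumptions: the programme adds dR to retention, a proportion w of the added patients is suppressed, and suppression in patients retained under either phase does not change.

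**Formulas for the treatment phase**
- Suppression among the retained = (R0·v + dR·w)/(R0 + dR)
- Retained-and-suppressed composite = R0·v + dR·w

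**Central case**, dR = 0.10 and w = 0.60
- Among the retained: (0.65 + 0.06)/0.86 = 0.71/0.86 = 82.6%, against 85.5%, a fall of about 3 points.
- Composite: 71%, against 65%, a rise of 6 points.

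**Range**

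| Added retention | Suppressed among added | Among retained | Change | Composite change |
|---|---|---|---|---|
| 5 points | 40% | 0.670/0.81 = 82.7% | −2.8 | +2.0 |
| 5 points | 70% | 0.685/0.81 = 84.6% | −1.0 | +3.5 |
| 10 points | 40% | 0.690/0.86 = 80.2% | −5.3 | +4.0 |
| 10 points | 70% | 0.720/0.86 = 83.7% | −1.8 | +7.0 |
| 10 points | 90% | 0.740/0.86 = 86.0% | +0.5 | +9.0 |

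The last row shows the condition. Once added patients are suppressed as often as the always-retained or more often, the reversal disappears.

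**Offset by a real gain.** If suppression among the always-retained rises by g, the restricted contrast is zero when g = dR·(v − w)/R0. In the central case this is 0.10 × (0.855 − 0.60)/0.76 = 3.4 points. A larger gain makes the restricted contrast positive.

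**Same check on the plan's own effect size.** Population and sample size gives 60% against 72% for the composite (0.72/0.60 = 1.2, as stated). Retention values are assumed:
- 70% to 85%: 0.60/0.70 = 85.7% and 0.72/0.85 = 84.7%, a change of −1.0 point.
- 70% to 82%: 85.7% and 0.72/0.82 = 87.8%, a change of +2.1 points.

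The same 12-point success on the primary outcome can thus come with a restricted contrast of either sign.

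**Patients left out.** If 76% of the 502 patients with PHQ-9 of 5 or more were retained, 502 × 0.76 ≈ 382 would be analysed and about 120 excluded.

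**The case against.** The best defence is that suppression among the retained is a legitimate component. It parallels the third UNAIDS target in the Background, which is suppression among those on ART. The composite equals retention times suppression among the retained, and the plan analyses all three. In the central case a reader would see the composite and retention rise beside the restricted figure, which limits the damage. This stands, and it is a reason to keep the restricted figure as description. It does not make that figure a test of H2.

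Three further limits also stand. The rise from 65% to 71% is the composite, not H2 regardless of lateness; some late patients would be suppressed, so the H2 levels would differ. The inputs come from another time point and a wider population. And the remedy has its own weakness: patients without a 6-month viral load will often be those lost to care, so weighting may fit poorly, while counting them as not suppressed brings H2 close to the composite.

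A reader might infer that depression remission (H5) has the same flaw, because the PHQ-9 is repeated only at ART visits. The article does not support that. Measures says only "Depression Remission will be defined as a PHQ-9 score < 5 at 6 months", nothing restricts remission to the retained, and the secondary-analysis paragraph does not list it. What remains is an unstated rule for missing 6-month scores, which an article may leave to the analysis plan.

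**Conclusion.** The point holds for H2. The Data analysis section conflicts with H2 and Table 2, and the restricted contrast does not test H2 because it conditions on an outcome that H3 expects to move.

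With 5 to 10 points more retention and 40% to 70% suppression among those added, the restricted contrast is −1.0 to −5.3 points while the composite gains 2 to 7. This rests on the stand-in inputs and on no effect in the always-retained.

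A reader might conclude that the programme will appear to worsen suppression. That goes too far: a wrong sign needs added patients to be suppressed less often than the always-retained, with too little gain among the latter to compensate. The primary analysis is not touched, since it counts patients who are not retained as failures. This is an inconsistency in a secondary outcome that should be corrected.

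**What to change.** In the Data analysis section, state that H2 is analysed by phase in all patients with PHQ-9 of 5 or more, and again in those with 10 or more. The outcome is a 6-month viral load below 1000 copies/mL, whether or not the patient was ever late.

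State the approach for patients without a result. One option is to count no result as not suppressed, with inverse-probability weighting as the alternative, so that each checks the other. Keep suppression among the retained, labelled descriptive and reported beside retention and the composite.

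The cost is a change of wording and some analysis code. No new data collection is needed, since viral load is already abstracted for every patient who screens positive. The downside is small: the H2 result will depend partly on the assumption made about missing viral loads.
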